**Study Protocol Approvals:**

**Population Council Institutional Review Board**

Original submission: August 14, 2014

Protocol approval: September 25, 2014

Amendment #1 approval: May 2, 2016

Amendment #2 approval: March 10, 2017

Amendment #3 approval: April 10^th^, 2018

1. **Summary of proposed research**

Overall Goal of the Project

The Adolescent Girls Initiative – Kenya (AGI-K), will deliver multi-sectoral interventions for 6,200 girls ages 11-14 in two marginalized areas of Kenya: 1) Nairobi slums and 2) Wajir County in Northeastern Kenya. The program will be implemented by a consortium of partners led by Population Council. The research partners include the African Population and Health Research Center (APHRC) and Itad. Save the Children will be the implementing partner in Wajir, while Plan International will oversee the intervention implementation in Nairobi. The interventions, which will run for two years, will comprise a combination of girl-level, household-level and community-level interventions across four sectors: education, health, violence prevention and wealth creation.

The overall goal of the interventions is to reduce adolescent fertility in the long-run by improving the wellbeing of girls in programme sites. A randomized controlled trial will be used to compare the impact of four different packages of interventions. In the Nairobi study, randomization to the four study arms will occur at the individual level. In Nairobi the design also includes an external control site. In Wajir, approximately 80 clusters (school-catchment areas) will be randomized to the four study arms. The research design will use both qualitative and quantitative methods to evaluate this impact. The quantitative study will consist of a baseline survey before the intervention is implemented, randomization to intervention packages, a Midterm survey with the same girls after the two-year intervention, and an endline survey two years post-intervention. Biomarker data, including testing for anaemia, Human Immunodeficiency Virus (HIV) and Herpes Simplex Virus 2 (HSV-2), will be collected at midterm and endline in the Nairobi sample. In-depths interviews will be conducted with a sample of program participants and key stakeholders halfway through the intervention and one-year post-intervention to better understand the causal mechanisms and the strengths and weaknesses of the intervention implementation. In addition, careful costing data will be collected to understand the cost of each intervention.

Risks and Benefits

Primary ethical concerns of this study include a) that participation in the study may put the respondent at risk of psychological trauma related to recounting violent or traumatic experiences, b) that this study includes minors, below the age of 18, and c) a risk of breach of confidentiality due to the collection of contact information and identifying information for future survey rounds. These risks are perceived to be minimal and steps will be taken to reduce the risks to participants.

Participants will receive no compensation for their participation in the study. In intervention sites, participants will benefit directly or indirectly from project interventions. All participants will be providing information that will directly inform the development of the interventions for adolescent girls in Kenya.

1. **Study Relationships/Related Project**

This project included a 9-month inception phase, from January to September, 2014. A protocol exemption for the inception phase was obtained on February 19th, 2014. This new protocol covers the entire implementation phase of the project, from October 1st, 2014 to October 31st, 2019. There are four sub-awardee institutions for this project. Additional information regarding each institution is provided below.

The African Population and Health Research Center, Inc. (APHRC) is an international non-profit, research institute that conducts high-quality research on urbanization, population, health and education issues facing sub-Saharan Africa. The Center was established in 1995 as a program of the Population Council and became an autonomous research institution in 2001. The role of APHRC in the consortium is to: 1) Collaborate on research design with Population Council, 2) Make recommendations on how the interventions will need to be designed and implemented given the research design, 3) Assist in development of survey tools and other research instruments and 4) Contribute to analysis and publications. The key personnel for AGI-K will be [name], [name] and [name].

Itad is a UK-based independent consultancy established in 1984. They have particular strengths in: evaluating large, multi-disciplinary programmes, policies and organisations; designing and implementing complex monitoring and evaluation (M&E) systems; and training, capacity building and lesson learning in M&E. The role of Itad in the consortium is to: 1) Conduct the cost benefit analysis and cost effectiveness component of study, including input into the research design and tools to ensure that appropriate costing data is collected, and 2) Provide expertise in value for money through the project period. The key technical personnel for Itad on AGI-K will be [name].

Save the Children is the world’s leading independent organization for children, creating lasting change in the lives of children in need in 120 countries around the world. They have been operational in Kenya since the 1950s, providing support to children through developmental and humanitarian relief programmes delivered both directly and through local partners. The role of Save the Children in the AGI-K consortium is to: 1) Lead implementation (either directly or through management of local partners) of the interventions in Wajir County, and 2) Supervise and monitor interventions in Wajir County, to ensure that the interventions are implemented with strict adherence to the research design. The key personnel for Save the Children on AGI-K will be [name].

Plan International (Plan) is an International Humanitarian, child-centred development organisation without religious, political or governmental affiliation. Plan has worked in Kenya since 1982, helping poor children to access their rights to health, education, sanitation and protection.  Plan strives to reduce poverty, raise children’s voices, support orphans and vulnerable children, and attend to those with special needs, such as the disabled. Plan’s role in the AGI-K consortium is to: 1) Lead implementation of the interventions in Nairobi County, and 2) Supervise and monitor interventions in Nairobi County to ensure that the interventions are implemented with strict adherence to the research design. The key personnel for Plan on AGI-K will be [name].

1. **Background**

Many adolescent girls in Kenya face considerable risks and vulnerabilities that affect their education status, health and general wellbeing. Therefore, it is critical to intervene at a time when girls are experiencing a myriad of challenges, but before those challenges have resulted in outcomes that may be irreversible. There is a wide range of research that has shown the benefits of education for girls. Documented benefits include delaying marriage, lowering family size, positive effects on a woman’s children and economic benefits to a woman, her family, and community. However, in addition, new thinking on education also posits that education alone is not enough to achieve ‘empowerment’, and that girls need critical thinking skills as well as changes in their enabling environment^^[[1]](#footnote-1)^^.

There is also evidence that economic assets, in addition to having value on their own, have benefits in other areas of women and girls’ lives. For example, girls who have fewer economic assets are more likely to have exchanged sex for money, gifts or shelter compared to girls with more assets^[[2]](#footnote-2)^; girls who received a cash benefit for schooling showed a decline in early marriage, teenage pregnancy and self-reported sexual activity^[[3]](#footnote-3)^; and adding a financial education component to a life-skills intervention resulted in significantly greater positive impact in changing sexual behaviours.^[[4]](#footnote-4)^ There is also evidence that while health interventions alone can improve health knowledge and attitudes, they are typically not sufficient to achieve health behaviour change. For example, lack of economic assets has been cited as a barrier to translating sexual and reproductive health knowledge into behaviour change, especially in adolescence, as girls are often financially dependent on men and therefore lose decision making power in their sexual relationships.^[[5]](#footnote-5)^ However, economic interventions on their own are not enough, and can even increase risk among adolescents^[[6]](#footnote-6)^ ^[[7]](#footnote-7)^, while programmes that have combined economic strengthening interventions with prevention of violence and health components have had a positive outcome on all three areas^[[8]](#footnote-8)^.

Therefore, the evidence points to multi-sectoral approaches for adolescent girls programming as a promising strategy for achieving high-level impact. With a comprehensive set of social, health, and economic assets built through a package of interventions, girls will be empowered to take more control over their decisions as to sexual partners, financial responsibilities, and health care.

The evidence, however, is lacking on which combination of interventions would be the most impactful. Further, in order to provide policy-relevant evidence that governments, donors, and other stakeholders can use to scale up successful packages for girls, it is critical to understand the costs attached to each package and which level of change can be expected for each financial input.

The main objectives of the research will be to determine: 1) Which combination(s) of interventions produce(s) the greatest change in the wellbeing of adolescent girls? and 2) What is the most cost-effective way to achieve the greatest impact for adolescent girls?

A randomized controlled trial design will be used to examine the impact of the intervention packages on various indicators of adolescent fertility and well being of girls over a four-year period (see Appendix A). The project will be implemented in Wajir County and Nairobi slums. Wajir County is located in the mainly rural, semi-arid region of Northern Kenya, and inhabited by a mainly pastoralist, Muslim population of Somali origin. The Nairobi slums represent the urban poor population of Nairobi. They are characterized by high population density, lack of public utilities and services, and high rates of migration.

In Nairobi, girls will be randomized to intervention packages at the individual level. All girls aged 11 to 14 residing within the study site will be listed and 3,000 girls will be selected based on a vulnerability index that excludes girls from high socio-economic status households. These girls will then be randomized to one of the four study arms. In addition, using the same procedure in an external control site, 750 girls will be interviewed but will not directly benefit from the interventions. In Wajir randomization will occur at the cluster level. Clusters will be defined as school-catchment areas of a fixed radius around a public primary school that includes all families sending girls aged 11 to 14 to the given public primary school. Based on power calculations, we will have 80 clusters (20 per arm), which will have approximately 3,200 girls in the given age group).

The intervention packages that will be tested are:

1. Violence Prevention
2. Violence Prevention + Education
3. Violence Prevention + Education + Health
4. Violence Prevention + Education + Health + Wealth Creation

The selection of package combinations was based on three factors: 1) prioritizing what component effects were important to isolate; 2) generating evidence on new interventions and new combinations of interventions for which there is none; and 3) testing packages with varying implementation costs.

The hypothesis is that this diverse asset base, once acquired, will lead to increased educational attainment, delayed childbearing and marriage, fewer unintended pregnancies, less experience of violence, and increased economic assets. Using both quantitative and qualitative data, we will also test the causal mechanisms driving the impact for each of the four intervention sectors, based on the hypotheses shown in Appendix B.

1. **Intervention**

Population Council has been involved in the design of the interventions, but the interventions will be implemented by Save the Children (Wajir) and Plan International (Nairobi). Information on these implementing partners has been provided in Section 3. All interventions will be implemented for a period of two years in research sites (see timeline in Appendix C). The beneficiaries will be girls selected for the research study as per the procedures described in Section 8.

In each sector AGI-K will implement one intervention so that it will be possible to attribute any change to that specific intervention component. In cases where more than one component is proposed, the rationale and evidence will be provided.

1. Violence Prevention

The violence prevention intervention will be a community level intervention using the community dialogues and contracts strategy.

AGI-K will adapt the UNDP/Concern model (described below), integrating promising approaches from the PC Guatemala and East Africa activities and will run this component for the full two years of the AGI-K intervention. It is envisioned that a core committee will be established within the first month. The committee will comprise religious leaders, community leaders, parents, teachers, and young men and women. This group will go through a facilitated process where they learn to identify the key issues in the community that lead to the under-valuing of girls, come up with a “contract” of steps to address those issues, and then carry out activities to implement the contract over the course of the intervention. A small amount of funds will be available for each community for implementation of the agreed upon steps. Careful monitoring will be done of the committee meetings and committee-led activities.

Community Conversations Model

Facilitators will be trained on the Concern International/UNDP-adapted Community Conversations (CC) model. The training will cover the development of facilitation skills required for social transformation, participatory tools needed to create community enlightenment and the classical process for guiding conversations. Each community conversations group will follow a manual that takes them through a structured process.

The manual for the CCs will include a schedule with specific session topics, activities and tools to be used during each session with the CC members. Through these guided sessions, the CC members will build relationships with each other, identify the major concerns related to violence against girls and the value of girls in their communities, explore the root causes of these concerns as well as the resources available to address them, make decisions and an action plan to address the concerns, implement their action plan using the CC fund, and reflect and review on their progress.

Figure 1. Community Conversations Framework

1. Education: Conditional Cash Transfer

The education intervention will be a conditional cash transfer based on 80% attendance over the course of a term. Attendance will be defined as attending the whole day of school. Girls who are both in and out of school at the start of the intervention will be eligible. There are four components to the transfer:

1. Fees: if applicable, to be paid at the start of each term, directly to the school, with the amount varying by site. The payment of first term fees in each year will be conditional upon enrolment. The payment of second and third term fees will be conditional upon attaining 80% attendance in the prior term (except for the fees for *first term of the program*, which will be paid conditional on enrolment, even though it will be the second term of the year).
2. Cash Transfer to Head of Household: to be paid twice per term, the first payment based on attendance during the first month of the term and the second payment will be made after the third month based on 80% attendance during the second and third months of the term. Each transfer will be 1750 KES, for a total of 3500 KES per term. This reflects 10% of monthly household consumption in Wajir and 15% for urban slums in Nairobi. This amount was determined based on needs assessments in the study communities, average household consumption in each site, and comparison to other education CCTs amounts^[[9]](#footnote-9)^.
3. Kits: at the start of each term, a girl will receive a schooling kit with the following items: 4 packs of sanitary towels, 2 panties, 1 small container of petroleum jelly, 1 bar of soap, 1 exercisebook, 1 pencil, 1 pen. The kit follows the same conditioning rules as the school fees.
4. School Incentive: In addition to the fees, each school will receive a top-up of 500 KES/ per girl enrolled in the CCT programme. This will be paid together with the fees payments at the start of the term.

Figure 2. AGI-K Education Cash Transfer Payment Schedule

In April 2015, eligible households will register for the cash transfer programme, providing details about the girl, school, and will provided with the payment details. At the time of registration, parents/guardians will also participate in a sensitization session about the importance and value of girls’ education. A household/girl will be eligible for the CCT for the entire two year period, regardless if she met the conditions the term before (e.g. she could receive the transfer during the first period of the term, but not the second if her attendance levels drop).

Cash transfer payments to the household will be made via Equity Bank. In Wajir, the payments will use the same infrastructure as the Hunger Safety Net Programme (HSNP), through which all households in Wajir have completed paperwork for account opening with Equity Bank. In Nairobi, the payments will use the Orphans and Vulnerable Children infrastructure – a cash transfer programme through which recipients have accounts with Equity Bank that operate special wallets to receive and transact with the transfer. Households that already have Equity accounts can have the payment wallet added to those accounts. Those that do not will be facilitated to open Equity accounts at the time of registration into the education CCT.

1. Health

The health intervention will follow the Council’s safe spaces model^[[10]](#footnote-10)^ in which girls will meet in groups once a week under the guidance of a female mentor from that community. Groups will be segmented by age (10-12 v. 13-14) in Nairobi and by schooling status in Wajir. The groups will follow a structured curriculum, but also allow time for open discussion. The curriculum will include topics on hygiene, nutrition, HIV/AIDS, sexual and reproductive health, communication/negotiation skills, gender norms, sexual and gender based violence, female genital mutilation/cutting (FGM/C), early marriage, leadership skills and relationships^[[11]](#footnote-11)^. The curriculum will be adapted from existing modules, used by the Council in similar interventions, for each geographical setting (Wajir/Nairobi slums) to ensure that the context is culturally-appropriate and acceptable by the community. In addition, certain sessions will be marked for the 13-14 year olds only if determined to be topics appropriate only for the older cohort. The information from the needs assessment, as well as previous partner experience working in these sites, will guide the decisions on which sessions are acceptable.

Groups will meet in spaces identified in the community as safe and appropriate for girls, which could be community halls, schools, churches, mosques, community leaders’ residences, and others. The groups will meet over the course of two years. This dose is in line with other similar programmes using the safe spaces model, as while one purpose is to deliver content, the other is to help girls build social assets such as friendships and adult mentor relationships. These relationships take time to build and past experience has shown that 18-24 months is the typical dose necessary for these effects to take root.

1. Wealth Creation

The wealth creation intervention will be composed of savings and financial education, layered on to the safe spaces groups. A financial education (FE) curriculum will be added to the group sessions for the girls in the wealth creation arm. These sessions will cover basic money management skills such as saving, budgeting, and differentiating between needs and wants. There are currently several curricula developed by Population Council and past partners for this age group, and they will need only minor adaptations for the urban site, with cultural adaptations for the northern site.

In the Wajir, girls will receive a homebank (piggybank) after the first unit of five to six financial education sessions. The homebank will have 300 Kenyan shillings (KES) in cash in it. The purpose of the cash is to allow girls to immediately put into effect the skills learned through the financial education sessions. The results of two recent literature reviews of evaluations of financial education suggest that financial education is most effective in achieving sustained behaviour change when the lessons learned can be put into practice at the time of the education^[[12]](#footnote-12)^ ^[[13]](#footnote-13)^. Therefore, the design includes an immediate opportunity for girls to start acting on savings goals and budgets. An additional 300 KES will be distributed at the start of the second year of the intervention for the same purpose.

In Nairobi, girls will be facilitated to open Smata Accounts with Kenya Postbank. These accounts, initially developed as part of the Youthsave programme^[[14]](#footnote-14)^, are unique from other “junior accounts” in the market in that these are accounts that are opened and managed by the girls themselves. Girls will need a co-signatory to open and make withdrawals from the account. The co-signatory will be a trusted adult above the age of 18 and selected by the girl. The programme will cover the 200 KES minimum operating balance, as well as make a 300 KES deposit at account opening, as well as at the start of the second year following the same reasoning listed above.

1. **Study Goals/Objectives**

The overall goal of the project is to reduce adolescent fertility in the long-run by improving the wellbeing of girls in programme sites.

The main objectives of this research will be to determine:

1. Which combination(s) of interventions produce(s) the greatest change in the wellbeing of adolescent girls?
2. What is the most cost-effective way to achieve the greatest impact for adolescent girls?

This IRB protocol requests approval of the overall AGI-K research design including activities to be implemented in 2016 and beyond. Specific forms and instruments for the household listing, school mapping, baseline survey components and monitoring data are submitted in full and we ask for approval to implement these activities immediately. In order to fully describe the AGI-K project, we are also including descriptions of the procedures for the midterm survey, endline survey, biomarker data collection, and qualitative survey but will submit amendments including the informed consent forms and instruments for these activities at a later date.

1. **Overview Table:**

|  | **Data Gathering Activities** | | | |
| --- | --- | --- | --- | --- |
| *Note: these are just examples and do not represent all possible study activities* | HH listing | School Mapping | Baseline Survey | Midterm Survey |
| **Study population** | Adult member in the household, all households in study sites in Nairobi | Administrators at all public primary schools in study sites | Girls aged 11 to 14 and adult member in household in all study sites | Girls aged 11-14 and adult member interviewed at baseline |
| **Sample size** | Approximately 60,000 households. | Approximately 400 schools | 3,200 girls & 3,200 parents/guardians in Wajir  3,750 girls & 3,750 parents/guardians in Nairobi | 2,150 girls & 2,150 parents/guardians in Wajir  3,093 girls & 3,093 parents/guardians in Nairobi |
| **Location of activity** | Household | School | Household | Household |
| **Timing** | October – December, 2014 | October – December, 2014 | January – March, 2015 | April – October, 2017 |
| **Method** | Short form | Observation & short form | Interview | Interview |
| **Informed Consent document (Appendix #)** | HH listing consent, Annex 1 |  | Parental permission form, and adolescent assent form, Annex 1 | To be submitted in amendment |
| **Study Instrument (Appendix #)** | HH listing form, Annex 2 | School mapping form, Annex 3 | Girls baseline survey, Annex 4 | To be submitted in amendment |

|  | **Data Gathering Activities (Continued)** | | | |
| --- | --- | --- | --- | --- |
| *Note: these are just examples and do not represent all possible study activities* | Endline Survey | Biomarker Data | Monitoring Data | Qualitative Study |
| **Study population** | Girls aged 11-14 and adult member interviewed at baseline | Girls participating in midterm and endline surveys ages 15 and above | Girls participating in the study and community dialogue members. | Girls selected from baseline sample, community dialogue members and key stakeholders |
| **Sample size** | 2,150 girls & 2,150 parents/guardians in Wajir  3,093 girls & 3,093 parents/guardians in Nairobi | 2,394 girls in Nairobi | 3,200 girls in Wajir  3,750 girls in Nairobi  Approximately 1,900 adults | In-depth interviews: 56 girls & 70 community members at each round |
| **Location of activity** | Household | Household | Household , school, program sites, financial institutions | Household |
| **Timing** | April – October, 2019 | April – June, 2017  April – June, 2019 | May 2015 – April 2017 | R1: May – August 2016 & R2: April – May, 2018 |
| **Method** | Interview | Finger-prick blood tests | Mobile phone apps, biometrics, and program documents | In-depth interviews |
| **Informed Consent document (Appendix #)** | To be submitted in amendment | To be submitted in amendment |  | Annex 8 |
| **Study Instrument (Appendix #)** | To be submitted in amendment | To be submitted in amendment |  | Annex 9 |

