**8. Data Collection Activity 4: Midterm Survey for Adolescent Girls**

**a. Subject Population**

- The sample will include all girls who participated in the baseline survey (2, 394 Kibera, 699 Huruma = 3, 093 in Nairobi and 2, 150 in Wajir). Girls will be located and asked to participate in a second interview.

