**8. Data Collection Activity 8: Monitoring Data**

**a. Subject Population**

- The study population is all girls who participate in the Baseline Survey and are randomized to the three arms that include direct program participation by girls. (2,250 Nairobi, 2,400 Wajir) and all adults (approximately 1,900 adults) who participate in the community dialogues (violence prevention intervention). Excluded are girls in the violence prevention only arm, who will not be directly participating in program activities and girls in the external control site in Nairobi.

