**APPENDIX A: AGI-K RANDOMIZED CONTROL TRIAL STUDY DESIGN**

**APPENDIX B. Causal Mechanisms by Which Interventions Might Affect Timing of Childbearing**

Arm 1

Arm 2

Arm 4

Arm 3

Endline

Endline

Endline

Midterm

Midterm

Midterm

WAJIR:

RANDOM ASSIGNMENT 80 Clusters (~3,200 girls)

NAIROBI:

RANDOM ASSIGNMENT 3,000 GIRLS

Baseline

Baseline

Baseline

Baseline

Midterm

Endline

Baseline

Midterm

Endline

NAIROBI

EXTERNAL CONTROL

SRH Knowledge & Social skills

Savings & Financial Education

Community Dialogues

Conditional Cash Transfer

Improved norms on timing of marriage

Reduced non-consensual sex

Increased enrollment & education attainment

Reduced risks (sex/marriage) driven by economic necessity

Reduced unprotected sex

Improved self-efficacy & decision-making

Causal Mechanism

Programme

Outcome

Legend Causal pathway in Wajir

Causal pathway in Nairobi

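### The amended protocol carries two unreconciled sample sizes per site, and the Wajir size it ties to power calculations is not the size the trial has

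*Protocol*

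**What the plan says.** **Planned sizes.** The Background section gives the Wajir design as "Based on power calculations, we will have 80 clusters (20 per arm), which will have approximately 3,200 girls in the given age group". For Nairobi it says that "3,000 girls will be selected based on a vulnerability index that excludes girls from high socio-economic status households", to be randomised to four arms, and that "in an external control site, 750 girls will be interviewed but will not directly benefit from the interventions". The Summary says the project "will deliver multi-sectoral interventions for 6,200 girls ages 11-14". The Appendix A design diagram shows "RANDOM ASSIGNMENT 80 Clusters (~3,200 girls") and 3,000 girls for Nairobi. The baseline column of the Overview Table and the Subject Population text of Activity 3 (Baseline Survey) give 3,200 for Wajir and 3,750 for Nairobi. Activity 8 (Monitoring Data) gives "2,250 Nairobi, 2,400 Wajir" for the three arms with direct programme participation.

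**Achieved sizes.** Activities 4 and 5 (Midterm and Endline Surveys) define the sample as every girl who took part at baseline and count them as "2, 394 Kibera, 699 Huruma = 3, 093 in Nairobi and 2, 150 in Wajir". The midterm and endline columns of the Overview Table use 2,150 and 3,093.

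**Related rules.** Activity 3 rules out replacing girls who cannot be interviewed, and places random assignment after the baseline survey. The protocol states no power, alpha, effect size, ICC or attrition allowance, and no realised number of clusters.

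**The concern.** Both sets of numbers stand in the current body text, so this is not a difference between an amendment log and the text it superseded. Later sections carry the achieved baseline counts, while the one sentence that links a sample size to power still carries the planned count. With no replacement, and with assignment following the baseline survey, the achieved baseline count is the sample available for comparing arms.

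The research objectives are to find which combination of interventions produces the greatest change and which is most cost-effective. The four packages are nested, so isolating a component means contrasting one arm with the next. Such increments may be small, and precision matters. A reader who relies on the Background section would credit those contrasts with more information than the achieved sample carries. Anyone using the monitoring counts as denominators would also start from the wrong base.

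**Working it through.** **1. Do the figures add up within each set?**
- Planned: 3,000 + 3,200 = 6,200; 3,000 + 750 = 3,750; 80 clusters × 40 girls = 3,200.
- Achieved: 2,394 + 699 = 3,093.
- Monitoring: ¾ × 3,000 = 2,250 and ¾ × 3,200 = 2,400, so these derive from the plan. On the achieved counts, with equal arms, they would be about 1,796 (¾ × 2,394 = 1,795.5) and 1,613 (¾ × 2,150 = 1,612.5).

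Each set is consistent in itself. The conflict is between the sets.

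**2. Planned against achieved**

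| Site | Planned | Achieved | Ratio | Shortfall |
|---|---|---|---|---|
| Wajir | 3,200 | 2,150 | 67.2% | 32.8% |
| Kibera | 3,000 | 2,394 | 79.8% | 20.2% |
| Huruma | 750 | 699 | 93.2% | 6.8% |
| Randomised sites together | 6,200 | 4,544 | 73.3% | 26.7% |

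That Kibera is the randomised site and Huruma the external control is inferred from the counts.

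**3. Can the planned size be reproduced?** No. None of the inputs to the power calculation is given.

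**4. Illustration under stated assumptions.** Assumed: two-sided 0.05, 80% power at the planned size, pairwise comparison of equal arms, normal approximation, and no attrition at either size. Girls are treated as independent in Nairobi. All 80 clusters, 20 per arm, are kept in Wajir.

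- Detectable difference = 2.80 × √(2 / n_eff), in SD units, where 2.80 = 1.96 + 0.84.
- Ratio r = √(n_eff planned / n_eff achieved).
- Power at the achieved size = Φ(2.80 / r − 1.96).

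*Nairobi.* Per arm, 3,000/4 = 750 planned and 2,394/4 = 598.5 achieved. r = √(750/598.5) = 1.119. Power = Φ(2.80/1.119 − 1.96) = 71%. The detectable difference goes from 2.80 × √(2/750) = 0.145 SD to 2.80 × √(2/598.5) = 0.162 SD.

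*Wajir.* Girls per cluster m: 3,200/80 = 40 planned and 2,150/80 = 26.9 achieved. n_eff per arm = 20m / (1 + (m − 1) × ICC).

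| ICC | n_eff planned | n_eff achieved | Power at achieved size | Detectable difference (SD) |
|---|---|---|---|---|
| 0 | 800 | 537.5 | 63% | 0.140 → 0.171 |
| 0.02 | 449.4 | 354.2 | 70% | 0.187 → 0.211 |
| 0.05 | 271.2 | 234.3 | 74% | 0.241 → 0.259 |
| 0.10 | 163.3 | 149.8 | 77% | 0.310 → 0.324 |
| 0.20 | 90.9 | 87.0 | 78% | 0.416 → 0.425 |

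If the planned size had 90% power instead, the achieved size gives about 83% in Nairobi and 76% (ICC 0) to 89% (ICC 0.20) in Wajir.

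**5. Attrition.** It must be applied to both sizes. In Nairobi, equal attrition cancels out of r, so 71% is unchanged as a comparison. In Wajir it shifts r slightly. With 20% lost at both sizes and ICC 0.05, m is 32 and 21.5, n_eff is 640/2.55 = 251.0 and 430/2.025 = 212.3, r = 1.087, and power is about 73% instead of 74%.

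**The case against.** The strongest reply is that the protocol states no power figure, so nothing has been contradicted. That stands in part: no loss of power can be demonstrated, only illustrated. The Background sentence can also be read as fixing 80 clusters from the power calculation and giving 3,200 girls as the expected yield. No passage says that the number of clusters changed, and in a cluster trial that number dominates. At ICC 0.05 or above, the illustrated Wajir loss is only about 2 to 6 points. The planned sizes may also have included an allowance for non-response or attrition; the protocol does not say.

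It can further be said that detectable effects, ICC and retention belong in a SAP, and that planned sizes are a legitimate design record. Both are fair, but they do not excuse leaving a power-linked size in the text beside achieved counts that differ from it by a third, with neither labelled.

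Three stronger readings are tempting and are not supported.
- A reader might infer that Nairobi's 3,000 rests on a power calculation. The text makes that link for Wajir only.
- A reader might infer that 100% follow-up is assumed, since the midterm and endline samples equal the baseline counts. Those sections say whom to approach, which suits the intent-to-treat analysis described under Activity 8. They do not forecast retention.
- A reader might infer that non-significant contrasts will be reported as showing no added effect. The protocol contains no such rule.

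**Conclusion.** The point holds as an inconsistency in the current text. Two sample sizes stand for each site without labels or reconciliation, and the Wajir size attached to the power calculations is one the trial did not reach. The shortfalls are firm: 33% in Wajir, 20% in Kibera and 27% across the randomised sites, the last two resting on the inference that Kibera is the randomised Nairobi site. The effect on power is conditional on the assumed 80% start, two-sided 0.05, 80 retained clusters and like-for-like attrition. On those terms it is about 9 points in Nairobi, and from about 17 points (ICC 0) to 3 points (ICC 0.10) in Wajir. This should be corrected, but it does not undermine the design.

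**What to change.** - Label the counts as planned or achieved wherever they appear: Summary, Background, Overview Table, Activities 3, 4, 5 and 8, and the Appendix A diagram. Keep the planned figures as the design record.
- Correct figures derived from the plan, such as 2,250 and 2,400 under Activity 8. The monitoring column of the Overview Table shows 3,200 and 3,750 and should be made to agree with Activity 8.
- State the realised number of clusters in Wajir, by arm, and confirm which Nairobi site was randomised.
- In the Background section, restate the size and its power basis as the minimum detectable difference for each pairwise contrast at the achieved sizes, giving the assumed ICC and retention. If the SAP already holds this calculation, a cross-reference would do.

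The cost is one recalculation and some wording. The stated detectable difference becomes slightly less favourable. Neither the sample nor the estimates change.
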